### Trial design {8}

To evaluate the efficacy of combining DBM with ADIM in patients with stroke, a randomized controlled trial utilizing a parallel design and employing an assessor-blinded methodology will be conducted. Participants are all inpatients of the Neurorehabilitation Department of Shanghai Second Rehabilitation Hospital who correspond with the inclusion criteria. The research projects are registered with the Chinese Clinical Trials Registry (ChiCTR-2100054897), and the study has been approved by the Ethics Committee of the Shanghai Second Rehabilitation Hospital (Shanghai, China). All participants will be informed of the trial and will sign a written informed consent form.

Patients who meet the inclusion criteria will be randomly grouped after basic data collection. This will be done by using a computer-generated random number table to randomly divide the subjects into a control group (receiving 4 weeks of conventional rehabilitation without other specific exercise interventions), and a study group (receiving 4 weeks of DBM + ADIM intervention alongside conventional rehabilitation) in a 1:1 ratio. Random numbers will be placed in opaque envelopes by independent persons not involved in this experiment to achieve allocation concealment. As this study uses an exercise intervention, it will be difficult to conceal the grouping from the therapist and subjects, but it will be possible to blind the outcome indicator measurer. We will arrange for a new assessor to replace the assessor familiar with allocation to achieve single blinding.

In this trial, a superiority trial framework has been established to examine a specific core training approach, with the aim of improving walking function in patients with stroke. The trial process includes an initial assessment one week before the start date, a final assessment post-trial, and a follow-up evaluation six months later. These evaluations serve the purpose of measuring treatment effectiveness, assessing potential side effects, and documenting relevant baseline data and clinical information of the participants. The study procedure is shown in Fig. 1 and the period of the study in Fig. 2. The program follows the principles of SPIRIT 2013.

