### Outcomes {12}

Participants will be assessed within 1 week of admission at baseline and the end of 4 weeks. The primary outcome is the 10 m maximum walking test (10MWT). Secondary outcome measures include the limits of stability test (LOS), Berg balance scale test (BBS), Functional Ambulation Categories test (FAC), Timed Up and Go test (TUG), trunk impairment scale test (TIS), ultrasound indicators of the diaphragm and transversus abdominis (UI), rhythmic weight shift test (RWS), walk across test (WA), Fugl-Meyer assessment of lower extremity (FMA-LE), and Barthel index of ADL test.

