### Procedure for unblinding if needed {17b}

If the following events occur during the trial, blinding will be lifted.:If the safety monitoring committee or data monitoring committee identifies an evident safety concern based on trial data that necessitate modifications to the trial or control group, or discontinuation of the trial, appropriate action will be taken.Immediate intervention will be warranted if a participant enrolled in the trial reports an apparent adverse reaction or side effect to the drug being tested.The results of the primary endpoint indicator of the trial have been sufficiently demonstrated that continued blinding is not required.

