There are still some limitations to this study due to some objective reasons: (1) strict control of inpatients in hospitals due to the epidemic situation, with a relatively homogenous source of subjects; (2) the ADIM technique is slightly difficult to operate and subjects have difficulty understanding the treatment; (3) unlike medication, rehabilitation training necessitates technical expertise and therapist guidance, making it challenging to implement double-blind protocols.

To adequately address the aforementioned limitations and minimize experimental errors, this study will implement the following measures: (1) it is difficult to conduct multicenter studies under strict epidemiological control, and when collecting cases in our hospital, we try to collect patients with stroke with different causes that meet the inclusion criteria; (2) multiple pre-intervention educations on ADIM techniques for therapists and subjects; (3) to minimize potential bias in trial outcomes, distinct personnel will be assigned for trial randomization and outcome assessment, ensuring the maintenance of single blinding.

Patients with stroke often have reduced trunk stability due to a lack of core strength, which in turn impairs walking function. To address this issue, our trial aims to focus on activating two critical core muscle groups, namely the diaphragm and transversus abdominis, through a combination of DBM and ADIM. Based on this training, which increases abdominal pressure and improves trunk stability, this trial will further investigate the extent to which this training improves balance and walking function in patients with early to mid-stroke.

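### A non-safety trigger requires the blind to be lifted mid-trial once the primary result is regarded as established; if assessments continue, they can be scored by an unblinded assessor because of that result

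*Protocol article*

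**What the plan says.** The procedure for unblinding {17b} opens with "If the following events occur during the trial, blinding will be lifted" and lists three events. The first two concern safety: a concern identified by a monitoring committee, and an adverse reaction in a participant. The third concerns efficacy: "The results of the primary endpoint indicator of the trial have been sufficiently demonstrated that continued blinding is not required".

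Trial design {8} says who is blinded: "it will be difficult to conceal the grouping from the therapist and subjects, but it will be possible to blind the outcome indicator measurer". The Discussion gives the purpose of that blind: "to minimize potential bias in trial outcomes, distinct personnel will be assigned for trial randomization and outcome assessment, ensuring the maintenance of single blinding".

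Outcomes {12} makes the 10 m maximum walking test primary and sets the assessment times: "Participants will be assessed within 1 week of admission at baseline and the end of 4 weeks". Trial design {8} adds a later visit: "a final assessment post-trial, and a follow-up evaluation six months later". Interim analyses {21b} plans one look at the primary endpoint, when half the patients have been randomised and have completed six months of follow-up. A statistician does the analysis and presents it to the data monitoring committee, after which the trial may be stopped or modified.

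**The concern.** Therapists and patients know the allocation throughout, so the assessor's blind is the only one that can be lifted. The Discussion relies on it as the safeguard against bias in outcome measurement. The third trigger withdraws that safeguard for a reason that protects no participant, and makes its withdrawal depend on the accumulating primary result.

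Measurement bias that enters only after a difference has been seen tends to reinforce that difference, including one that arose by chance. The measures at risk are the walking test and the rated scales, such as the Berg balance scale, the trunk impairment scale and the Fugl-Meyer lower-extremity score. The clause gives no level of evidence, no decision-maker and no limit on who is unblinded.

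**Working it through.** **Reading the sections together.**

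1. The list in {17b} governs events during the trial, and the listed consequence is mandatory.
2. The third event is defined by the primary result, not by safety.
3. By {8}, the only blinded role is the outcome assessor.
4. By {21b}, stopping after the interim is possible but not required. No section says that assessments still due would go to a blinded assessor.
5. If the trial continues, those assessments can therefore be scored unblinded. This conflicts with the Discussion's aim.

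**How many assessments could be exposed at the planned interim.** Inputs are 42 patients (Sample size {14}) and one year of recruitment (Recruitment {15}). Uniform accrual is assumed, so patient i enters at month i × 12/42.

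- Patient 21 enters at month 6.0. Six months of follow-up ends at month 12.0 if counted from randomisation, or at 12.0 + 4/4.345 = 12.92 if counted from the end of the four-week treatment.
- Four-week assessments fall at entry + 0.92 months. Those still due at month 12.0 belong to patients who entered after month 11.08, that is i > 38.8, which is patients 39 to 42, or 4 assessments. At month 12.92 none remain.
- Six-month assessments outstanding: 42 − 21 = 21 in either case.
- If accrual took 18 to 24 months, 7 to 13 four-week assessments and again 21 six-month assessments would remain.

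The trigger is not tied to this look. If it were invoked earlier, more would be exposed.

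**Illustrative effect on type I error.** The analysed sample is the plan's own 36. With effect size 1.1327272, two-sided 5% and 1:1 allocation, the noncentral t gives power 0.893 at 17 per arm and 0.910 at 18 per arm, so 36 is reproduced.

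The simulation assumes no true effect, standard normal outcomes, 18 v 18 and one final two-sided 5% t-test. If the first 9 v 9 favour the study arm at the trigger level, a shift b (in SD) is added to the exposed later study-arm values. Trigger level, shift and exposure are all assumptions. I reran it with 400,000 trials per scenario.

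| Exposed study-arm values | Trigger | b = 0.2 | b = 0.3 | b = 0.5 |
|---|---|---|---|---|
| 9 of 18 | p<0.05 | 5.3% | 5.5% | 6.0% |
| 9 of 18 | p<0.20 | 6.2% | 6.9% | 8.3% |
| 2 of 18 | p<0.05 | 5.1% | 5.2% | 5.2% |
| 2 of 18 | p<0.20 | 5.2% | 5.3% | 5.5% |

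The lower rows match the planned interim under one-year accrual: up to 4 outstanding four-week assessments is about 2 per arm. Across variants of that case, a 0.3 SD shift gives about 5.0 to 5.6%. The half-exposed rows would apply to earlier use of the trigger, or to a comparison made on six-month values, since 21 of 42 would be outstanding.

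As a sensitivity check, drift towards whichever arm leads (0.25 to 0.5 SD, half exposed) gives 5.9 to 6.9% at p<0.05 and 8.0 to 11.8% at p<0.20.

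**The case against.** The best defence is that the clause describes ordinary code-breaking once the result is settled. On that reading the trial stops and nobody is scored unblinded. {21b} does allow stopping. However, the list is headed as events during the trial, and the clause itself speaks of continued blinding. It is not worded as an end-of-trial step, and stopping is not required. The defence shows that harm is conditional; it does not remove the rule.

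Four further points stand and limit the finding:

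- A reader might infer that later patients will be scored by an unblinded assessor as soon as a trend favours one arm. The document does not say this. It does not state that assessments continue after the trigger, and its wording is a claim of demonstration, which is stronger than a trend. A p<0.20 trigger is therefore a lenient assumption.
- The only access to results by arm that the article describes is the planned interim, by a statistician for the committee. The clause does not refer to that look, but nothing shows anyone else viewing results by arm.
- A reader might take a type I error near 7% as the size of the problem. That needs a lenient trigger and half the primary values still to come. The planned interim under one-year accrual leaves far fewer four-week values. Even with half exposed, a p<0.05 trigger favouring the study arm fires in only about 2.5% of null trials, so overall error moves little.
- Patients and therapists are unblinded throughout. Assessor blinding therefore does not remove effects of their own effort or expectation, and the article describes no encouragement procedure for the walking test.

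**Conclusion.** The point holds as a conditional risk. The article states a rule that lifts its only blind on the strength of the primary result, with no threshold and no stated link to the interim. If the trial then continues, the rule permits result-dependent measurement bias, contrary to the article's own aim.

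The likely effect on the four-week primary is small if the trigger is used only at the planned interim and recruitment takes the planned year. The exposure then falls mainly on the 21 six-month assessments. With half the primary values exposed, the inflation is modest under a p<0.05 trigger and larger under a looser one. None of these sizes comes from the document, and all depend on the assumed accrual, trigger and shift. The case for change rests on the logic of the rule and the low cost of removing it, not on any one simulated figure.

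**What to change.** Delete the third event from {17b} and add: *Outcome assessors remain blind to allocation until the last assessment of the last participant has been recorded and the database is locked, whatever any interim result shows. Interim results by arm are seen only by the data monitoring committee and its statistician.*

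The two safety triggers are untouched by this point. The cost is a short amendment, with no additional patients, visits or staff. It brings {17b} into line with {8} and the Discussion.

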## Data collection and management

### Plans for assessment and collection of outcomes {18a}

All information about the patient shall be recorded by the assessor staff in a true, accurate, and timely manner on the case report form (CRF). The data manager will handle the relevant data exclusively and maintain strict confidentiality of participants’ personal information. To ensure patient privacy, all data will be identified using the subject number. Data will not be discussed without the researcher’s permission. At the end of the course, the assessor should submit a CRF promptly and submit a summary of the trial as required. A monitor will be specified by the research center to review the completeness and precision of the CRF.

Significantly, ultrasonic testing represents a pioneering measurement technique within the realm of medical assessment, warranting comprehensive elucidation of its testing methodologies:Using a Siemens Acuson Sequoia 512 compound B/M ultrasound, a wide-bore high-frequency line array probe with a frequency of 12–17 MHz was selected to record the B-mode ultrasound images.

The participant assumes a supine position with the knees in a relaxed and extended state. To obtain an intercostal view, the transducer is positioned longitudinally along the anterior axillary line on both sides, approximately at the 9th intercostal space. Evaluation takes place while the subject engages in forceful breathing, specifically during maximal inspiration. Notably, the diaphragm exhibits a distinctive three-layer structure, comprising two hyperechoic lines of pleura and peritoneum, flanking a central hypoechoic muscular region. Measurements of diaphragmatic thickness are obtained at the conclusion of both maximal inspiration and expiration. To ensure accuracy, three images are acquired and subsequently averaged.

Measurement of transversus abdominis thickness entails positioning the participant in a supine posture, with the abdomen in a relaxed state and breathing maintained at a calm pace. To establish a central placement, point for the probe, the examiner creates a vertical line originating from the unilateral anterior superior iliac spine, intersected by a horizontal line drawn at the level of the umbilicus. Once the probe is appropriately positioned, adjustments are made to capture images encompassing the three distinct layers of the abdominal muscles. It is important to note that image acquisition will be performed both at the end of calm breathing and during the peak activation of the ADIM.

### Plans to promote participant retention and complete follow-up {18b}

The present study proposes several viable avenues for enhancing participant recruitment and bolstering follow-up rates. Additionally, the protocol entails the meticulous collection of outcome data for those individuals who deviate from the designated treatment regimen or withdraw from the study group altogether:A transparent and easily comprehensible trial prospectus, accompanied by a comprehensive informed consent form, is imperative for any clinical trial. The trial prospectus must furnish an unambiguous and detailed account of the trial’s purpose, methodology, and rights of the participants, to ensure that the participants are privy to the full corpus of information related to the trial’s conduct. Furthermore, the informed consent form must explicate participant obligations and rights, while concurrently clarifying any ambiguities that may arise during the trial.Friendly subject recruitment and screening process. During the recruitment and screening process, explain and ask questions in a friendly and welcoming manner to help subjects dispel their doubts and concerns while minimizing the cost of time and effort to the subjects.The habitual persuasion of patients to undergo the intervention amidst the clinical trial.Developing a rigorous and efficacious follow-up program.Collection of outcome data after subjects have withdrawn or changed treatment regimens: If the patient has been receiving the intervention for more than 2 weeks, the patient’s data should still be notes and statistics.

### Data management {19}

During the test, what is recorded in the CRF should be true and accurate. The CRF must comply with the following criteria:The data must be recorded in black marker and the assessor’s signature is required;If the patient has been receiving the intervention for more than 2 weeks, the patient’s data should still be notes and statistics;If there is an error in the record that needs to be rectified, the recorder should draw a horizontal line under the original record and then sign the revision with the date of the correction.

Note that it is important to ensure that the original record is identifiable after the correction is made.

### Confidentiality {27}

Details of the operation are in the “Plans for assessment and collection of outcomes {18a}” section.

### Plans for collection, laboratory evaluation, and storage of biological specimens for genetic or molecular analysis in this trial/future use {33}

As this study did not involve biological specimen collection, laboratory analysis, or storage, this item was not applicable to our trial.

## Statistical methods

### Statistical methods for primary and secondary outcomes {20a}

Statistical analysis of research data will be performed by health statisticians and major researchers using SPSS 24.0. The statistical tests will all be two-sided. The level of statistical significance will be set at 5%. The measured data will be presented as mean ± standard deviation. Paired *t*-tests will be used for within-group controls before and after the trial. Comparisons between the two groups will be made using *t*-tests or rank sum tests.

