### Sample size {14}

The study was a randomized controlled trial, with the 10 m maximum walking speed of the study participants as the main outcome indicator observed. The study was found by sample estimation with the G*Power 3.1 software, which, combined with previous studies, resulted in an effect size of 1.1327272, a power value of 0.9, and a significance level of *a* = 0.05, giving a sample size of 36 cases. Considering that there may be a 15% attrition rate during the trial, the required sample size was obtained. The final sample size was calculated to be 42 cases.

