### Methods for additional analyses (e.g., subgroup analyses) {20b}

In this trial, our primary objective was to assess the effectiveness of a novel core training approach for patients with stroke compared to a conventional training approach, using a simple comparative trial design to establish the superiority of one treatment group over the other. As the trial design is straightforward and robust, with no apparent confounding factors or subgroups, no additional subgroup or correction analysis is deemed necessary.

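### The between-group analysis of 10MWT uses no baseline covariate and adjustment is declared unnecessary for a reason that does not apply; ANCOVA on the baseline value already collected would gain precision at almost no cost

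*Protocol article*

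**What the plan says.** All references are to the protocol article.

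- *Statistical methods for primary and secondary outcomes {20a}*: "Comparisons between the two groups will be made using *t*-tests or rank sum tests". "The statistical tests will all be two-sided", at the 5% level. No covariate is named, and nothing says whether the compared quantity is the 4-week value or the change from baseline. The same section adds: "Paired *t*-tests will be used for within-group controls before and after the trial".
- *Methods for additional analyses {20b}*: the design is described as simple and robust, "with no apparent confounding factors or subgroups, no additional subgroup or correction analysis is deemed necessary".
- *Outcomes {12}*: 10MWT is the primary outcome, and participants are assessed at baseline and at the end of 4 weeks. A baseline value of the primary outcome is therefore available.
- *Sample size {14}*: the calculation "resulted in an effect size of 1.1327272, a power value of 0.9, and a significance level of *a* = 0.05, giving a sample size of 36". An allowance for 15% attrition then raises the total to 42.
- *Trial design {8}*: computer-generated random numbers, "alongside conventional rehabilitation) in a 1:1 ratio", within a superiority framework. No stratification is described.

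**The concern.** Section {20b} justifies having no correction analysis by the absence of apparent confounders. Because that sentence speaks of confounding factors, covariate adjustment is the natural reading of correction analysis, although the wording is loose. Randomisation already deals with confounding in expectation. Adjusting for a baseline measure of the outcome does two other things: it removes the part of the outcome variance that baseline predicts, and it corrects the estimate for whatever baseline difference chance has produced. The stated reason addresses neither.

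Both matter in a trial with about 18 evaluable patients per arm, ages 40 to 85, and haemorrhage and infarction combined. At stake is precision in the primary comparison, and therefore the chance of detecting an effect smaller than the very large one assumed. The validity of the test is not at stake.

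**Working it through.** **Inputs from the protocol article.** Effect size d = 1.1327272, power 0.9, alpha 0.05, N = 36, attrition 15%, final N = 42 (*Sample size {14}*); two-sided tests ({20a}); 1:1 allocation ({8}).

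**Inputs assumed.** The baseline to 4-week correlation r is not given, so I take 0.3 to 0.8. An effect of 0.8 SD is used only to show what happens if the stated effect is too optimistic. SDs are taken as equal at baseline and 4 weeks, and d is taken in SDs of the 4-week value. The article does not say which SD its effect size refers to.

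**Step 1. Reproduce the plan's figure.** Two-sample t-test, non-centrality d·√(n/2), df = 2n − 2:
- n = 17 per arm: power 0.893.
- n = 18 per arm: power 0.910, so N = 36 as stated.
- Attrition: 36 × 1.15 = 41.4, giving 42; 36 / 0.85 = 42.4, giving 43. In the other direction, 42 × 0.85 = 35.7, about 36 evaluable.

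The sizing is that of an unadjusted two-sided t-test, and it reproduces.

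**Step 2. Variance of each analysis, relative to a t-test of 4-week values.**
- Change-score t-test: 2(1 − r).
- ANCOVA: 1 − r².
- ANCOVA relative to change score: (1 − r²) / [2(1 − r)] = (1 + r)/2, so the saving is (1 − r)/2.

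| r | Change score, 2(1 − r) | ANCOVA, 1 − r² | ANCOVA saving vs 4-week values | ANCOVA saving vs change |
|---|---|---|---|---|
| 0.3 | 1.40 | 0.91 | 9% | 35% |
| 0.5 | 1.00 | 0.75 | 25% | 25% |
| 0.7 | 0.60 | 0.51 | 49% | 15% |
| 0.8 | 0.40 | 0.36 | 64% | 10% |

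**Step 3. Power with 18 evaluable per arm.** Divide d by the square root of the factor above; ANCOVA has one fewer degree of freedom (33 instead of 34).

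| r | d = 1.13: 4-week values | d = 1.13: change | d = 1.13: ANCOVA | d = 0.8: 4-week values | d = 0.8: change | d = 0.8: ANCOVA |
|---|---|---|---|---|---|---|
| 0.3 | 0.910 | 0.797 | 0.933 | 0.645 | 0.504 | 0.685 |
| 0.5 | 0.910 | 0.910 | 0.968 | 0.645 | 0.645 | 0.767 |
| 0.7 | 0.910 | 0.989 | 0.996 | 0.645 | 0.853 | 0.903 |
| 0.8 | 0.910 | 0.999 | >0.999 | 0.645 | 0.958 | 0.973 |

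The effect detectable with 90% power is 1.11 SD unadjusted. With ANCOVA it is 1.06, 0.96, 0.80 and 0.67 SD at r = 0.3, 0.5, 0.7 and 0.8.

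*Caveat on the ANCOVA columns.* They leave out the small expected cost of estimating the slope, a variance factor of 1 + 1/(2·18 − 4) = 1.031. At r = 0.3 the variance factor becomes 0.91 × 1.031 = 0.938, a saving of about 6% instead of 9%. At r = 0.8 it becomes 0.36 × 1.031 = 0.371, a saving of about 63%. The ordering of the three analyses does not change anywhere in the tables.

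**Step 4. Chance imbalance.** The baseline mean difference has standard error √(2/18) = 0.333 SD. A difference above 0.5 SD in either direction lies 0.5/0.333 = 1.5 standard errors out, with probability 0.134. At r = 0.7, an imbalance of 0.5 SD shifts the expected difference in 4-week values by 0.7 × 0.5 = 0.35 SD and the difference in changes by (0.7 − 1) × 0.5 = −0.15 SD. ANCOVA removes the expected shift in both cases.

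**The case against.** The strongest reply is that the planned analysis is valid. A two-sample t-test after randomisation is unbiased and controls type I error, and the sample size was computed for that test. At the stated effect it has its 90% power without any covariate. This stands: adjustment here is an efficiency gain and does not repair an invalid test.

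Second, the size of the gain depends on a correlation that the article does not give. At r = 0.3 the gain over a t-test of 4-week values is small (0.91 to 0.93 at the stated effect). This also stands, and it is why a range is shown.

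Three stronger readings are tempting, and the article does not support them.

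- *That the between-group test ignores baseline.* Section {20a} does not say so. A t-test of changes would use baseline in part, and at r = 0.8 ANCOVA would then save only 10% of the variance.
- *That naming two tests inflates type I error.* Taking the smaller of the two p-values would raise it to about 6%, but nothing says that this is intended. The sentence covers primary and secondary outcomes together, some of them ordinal scales such as FAC, and the rule for choosing may stand in a fuller document.
- *That within-group paired tests will serve as evidence of efficacy.* They are listed beside a between-group comparison, and both {8} and {20b} frame superiority as one group against the other. A label calling them descriptive is worth adding, but their presence is not an error.

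**Conclusion.** The point holds as a recommendation to improve a stated method. The article specifies a comparison without a covariate and sets adjustment aside for a reason that does not bear on why one adjusts in a randomised trial. This is a choice made in the text, so it is not merely a detail left to an analysis plan.

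Over the assumed r of 0.3 to 0.8, ANCOVA is more precise than either version of the t-test, but by very different amounts. The saving against 4-week values is least at low r, and the saving against changes is least at high r. ANCOVA does not require anyone to know r in advance to choose well. The practical value lies in effects below the planned 1.13 SD, as the 0.8 SD columns show. No claim is made that the trial is underpowered on its own assumptions.

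The figures rest on the assumed correlation, equal SDs at the two visits, an effect size expressed in SDs of the 4-week value, and 36 evaluable patients out of 42 enrolled.

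**What to change.** 1. In {20a}, name one primary analysis: ANCOVA of 4-week 10MWT speed on group and baseline 10MWT speed, reporting the adjusted mean difference with its 95% confidence interval. This also settles whether 4-week values or changes are compared.
2. Keep the rank sum test for 10MWT as a sensitivity analysis.
3. Use the same model, each with its own baseline value, for the continuous secondary outcomes.
4. In {20b}, remove the words *or correction*. The statement that no subgroup analysis is planned can stay.
5. As a wording note in {20a}, label the within-group paired comparisons as descriptive.

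The sample size need not change. The cost is protocol wording and one degree of freedom, and no new data are needed. The article reports that the trial is still recruiting, so the change should be made and dated before any comparison by group.
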